## Abstract

**Introduction:**

Dyslipidemia accompanied by metabolic syndrome substantially elevates cardiovascular risk by clustering multiple risk factors, including abdominal obesity, hypertension, hyperglycemia, and atherogenic dyslipidemia. The prevalence of both conditions is rising in Korea, underscoring the need for effective and metabolically safe lipid-lowering therapy. LivaloZet^®^ Tablet (pitavastatin/ezetimibe fixed-dose combination) addresses this need by combining complementary cholesterol-lowering mechanisms with the glucose-neutral profile of pitavastatin.

**Methods and analysis:**

The PIVOT study is a multi-center, non-interventional, prospective observational study enrolling up to 10,000 Korean adult patients with dyslipidemia accompanied by metabolic syndrome who have been prescribed LivaloZet^®^ Tablets (pitavastatin/ezetimibe 2/10 mg or 4/10 mg) by their treating physician as part of routine clinical care. Metabolic syndrome is defined according to the modified NCEP-ATP III criteria for the Asian population. Assessments are conducted at baseline, Week 24, and Week 48. The primary endpoint is the percent change in low-density lipoprotein cholesterol (LDL-C) from baseline at Week 24. Secondary endpoints include LDL-C changes at Week 48, changes in the full lipid panel, and LDL-C target achievement rates by cardiovascular risk group. Exploratory endpoints encompass glucose metabolism parameters (HbA1c, HOMA-IR, HOMA-β), medication adherence and persistence, and high-sensitivity C-reactive protein. Safety is assessed through adverse events, laboratory tests, and vital signs, including systematic monitoring of AST, ALT, and creatine kinase for statin-related hepatotoxicity and myopathy. The study was approved by the Institutional Review Board of Chungnam National University Hospital (2025-07-065) and is registered at ClinicalTrials.gov (NCT07523971).

**Discussion:**

The PIVOT study will generate prospective large-scale real-world evidence on the LDL-C-lowering effectiveness and safety patterns associated with use of a pitavastatin/ezetimibe fixed-dose combination in Korean patients with dyslipidemia accompanied by metabolic syndrome. The inclusion of glucose metabolism and inflammatory markers will provide descriptive information on the metabolic safety profile of this regimen. As a non-randomized, single-arm observational study, this design cannot establish causal effects or comparative efficacy versus other lipid-lowering regimens. Findings should be interpreted descriptively, acknowledging potential confounding by indication, selection bias, and inter-laboratory variability.

## Introduction

1

Dyslipidemia is defined as a condition in which low-density lipoprotein cholesterol (LDL-C) is elevated, triglycerides (TG) are elevated, or high-density lipoprotein cholesterol (HDL-C) is reduced in the blood (1). Since dyslipidemia acts as a major risk factor that can lead to cardiovascular disease and progress to life-threatening conditions, managing blood lipid levels is of critical importance (1–4). In particular, patients with dyslipidemia accompanied by metabolic syndrome carry multiple cardiovascular risk factors - including obesity, hypertension, hyperglycemia, and various types of dyslipidemia - making rigorous lipid management essential for the prevention of cardiovascular disease and improvement of prognosis (1, 5, 6).

According to the recently published 2024 Dyslipidemia Fact Sheet and Metabolic Syndrome Fact Sheet, the prevalence of dyslipidemia among Korean adults aged 20 years and older was 37.5%, while the prevalence of metabolic syndrome among Korean adults aged 19 years and older was 24.9%; both conditions showed an increasing trend in prevalence with age (7, 8). Considering the rapid aging of Korea’s population, the number of patients with dyslipidemia accompanied by metabolic syndrome is expected to continue rising, making aggressive lipid control increasingly important (9).

Among the various lipid-lowering agents used in pharmacotherapy for dyslipidemia, statins are generally administered once daily, offer excellent LDL-C-lowering efficacy, and have a relatively favorable safety profile, making them the first-line treatment (9). Statins competitively inhibit the reductase of 3-hydroxy-3-methylglutaryl-coenzyme A (HMG-CoA), a cholesterol precursor, thereby reducing hepatic cholesterol synthesis, upregulating LDL receptor expression, accelerating hepatic uptake of circulating cholesterol, and decreasing plasma total cholesterol (TC) and very low-density lipoprotein (VLDL) (9, 10). However, concerns exist about dose escalation of statins until LDL-C reaches target levels, due to safety issues including dose-dependent hepatotoxicity and the risk of rhabdomyolysis (11). Therefore, in patients requiring a potent LDL-C reduction or in whom high-dose statin therapy is not feasible due to adverse effects, combination therapy with ezetimibe is recommended (9, 12, 13).

Ezetimibe is a selective cholesterol absorption inhibitor that acts on the Niemann-Pick C1-Like 1 (NPC1L1) protein, a cholesterol transport carrier in the intestinal villi, without affecting the absorption of bile acids, fatty acids, triglycerides, or fat-soluble vitamins, thereby inhibiting the absorption of both dietary cholesterol and biliary cholesterol undergoing enterohepatic circulation (14, 15). As monotherapy, ezetimibe reduces LDL-C by approximately 17–20%, which is weaker than statins; however, when combined with a statin, complementary effects arise from the two distinct mechanisms of action - namely, statin-mediated inhibition of endogenous cholesterol synthesis and ezetimibe-mediated inhibition of exogenous cholesterol absorption (15–20). Given these advantages, combination therapy with a statin and ezetimibe has been deemed effective and safe for reducing LDL-C levels, leading to the development and commercialization of multiple fixed-dose combination products.

The product evaluated in this observational study, LivaloZet^®^ Tablet, is a fixed-dose combination of pitavastatin and ezetimibe that was approved and marketed in Korea in 2021 for primary hypercholesterolemia. LivaloZet^®^ Tablet is a lipid-lowering agent indicated for patients requiring potent LDL-C reduction or those for whom high-dose statin therapy is not feasible due to adverse effects. Furthermore, since pitavastatin is known to have a relatively neutral adverse effect profile on glucose metabolism compared with several other statins (21–23), LivaloZet^®^ Tablet is expected to be a useful therapeutic option for lipid management in patients with metabolic syndrome who have or are at risk of hyperglycemia (21–23). Therefore, this study aims to describe the LDL-C-lowering effectiveness and safety profile of LivaloZet^®^ Tablet in Korean adult patients with dyslipidemia accompanied by metabolic syndrome under real-world conditions.

## Methods and analysis

2

### Study design

2.1

This study is a multi-center, non-interventional, prospective observational study conducted in routine clinical practice. As a non-interventional study, treatment decisions—including drug selection, dose, dose changes, and discontinuation—are made by the treating physician independently of the study, in accordance with their usual clinical judgment and the approved product label. The study participants are patients with dyslipidemia accompanied by metabolic syndrome. The objective of this study is to describe the LDL-C-lowering effectiveness and safety profile associated with the use of LivaloZet^®^ Tablets in patients with dyslipidemia accompanied by metabolic syndrome in real-world Korean clinical settings. The products under evaluation are LivaloZet^®^ Tablets 2/10 mg (pitavastatin calcium/ezetimibe 2/10 mg) and LivaloZet^®^ Tablets 4/10 mg (pitavastatin calcium/ezetimibe 4/10 mg). Dose selection (2/10 mg vs 4/10 mg) is made by the treating physician based on the patient’s cardiovascular risk category, baseline LDL-C level, prior lipid-lowering treatment history, and clinical judgment. Dose modifications, including up-titration, down-titration, or discontinuation, are permitted at any time according to routine clinical practice and will be recorded.

The flowchart of the study is shown in **Figure 1**. Participants who provide written informed consent will be assigned a participant identifier and assessed for eligibility based on the inclusion and exclusion criteria. Those eligible based on the inclusion and exclusion criteria will have scheduled visits at Week 24 (Visit 2) and Week 48 (Visit 3) from the baseline visit (Visit 1). Participants with any unresolved adverse events (AEs) at the end of study (EOS) visit will be followed until resolution, stabilization, or for a minimum of 4 weeks after the EOS visit, whichever is later, with extended follow-up at the investigator’s discretion for serious or clinically significant events. A detailed schedule of enrollment and assessments is presented in **Table 1**.

**Figure 1 f1:**
[figure not shown]
The flowchart of the study.

**Table 1 T1:** Participant timeline: schedule of enrollment and assessments.

Visit	Visit 1 (Baseline)	Visit 2	Visit 3 (EOS)	UV
Day (Week)	**D1 (W0)**	**D169 (W24)**	**D337 (W48)**	**-**
Visit window	**-**	**-2M~+1M**	**-2M~+1M**	**-**
Written informed consent¹)	●			
Demographic information²)	●			
Baseline disease information³)	●			
Cardiovascular risk classification	●			
Medical history^4^)	●			
Prior/concomitant medication^5^)	●	●	●	○
Physical examination	●	●	●	○
Vital signs (blood pressure, pulse rate, body temperature)	●	●	●	○
Physical measurement^6^)	●	○	●	○
Serum lipids^7^)	●	●	●	○
Blood glucose and glucose metabolism parameters^8^)	○	○	○	○
Cardiovascular risk biomarker (hs-CRP)^9^)	○	○	○	○
Blood chemistry (AST, ALT, CK)¹^0^)	●	●	●	○
Apolipoprotein B (ApoB)¹¹)	○	○	○	○
TLC education and checking	●	●	●	○
Inclusion and exclusion criteria checking	●			
Participant enrollment	●			
IP prescription/administration checking	●	●	●	○
Medication adherence & persistence¹²)		●	●	○
AEs¹³)		●	●	○

AEs, Adverse events; EOS, end of study; TLC, Therapeutic Lifestyle Change; UV, unscheduled visit.

**●** To be conducted in all participants enrolled in the study.

**○** Optional items for which information will be collected only if test results are obtained in routine clinical practice. Information will not be collected if there are no test results.

^1)^All study related procedures should be performed after written informed consent is obtained; After informed consent is obtained, a participant identifier will be assigned.

^2)^Date of birth, age, sex, pregnancy/breastfeeding, and smoking history will be collected.

^3)^Date of initial diagnosis of dyslipidemia/metabolic syndrome, presence of pre-diabetes/diabetes, date of initial diagnosis of diabetes, family history of premature coronary artery disease, presence of hypertension, and presence of target organ damage will be collected. If classification of cardiovascular disease risk groups has been previously performed, or if the necessary information for classifying cardiovascular disease risk groups is available, allowing the investigator to classify the risk groups directly, the relevant information will be collected. Cardiovascular risk classification (per **Table 2**) will be assigned at Visit 1 by the treating investigator (Section 2.3) and will not be re-assigned during follow-up.

^4)^Medical history (including surgical/procedure history) within 12 weeks prior to Visit 1 will be collected. For medical history relevant to the inclusion and exclusion criteria, information throughout lifetime will be collected, unless otherwise specified.

^5^Medication information on lipid regulators, antidiabetics, and other drugs will be collected. Drugs administered within 4 weeks prior to Visit 1 will be collected as prior medication. If there is a history of treatment with lipid regulators within the predefined duration of information collection for prior medication, medication information on lipid regulators within 8 weeks prior to Visit 1 will be collected. In addition, if results of prior serum lipid or blood glucose and glucose metabolism parameter tests are used as baseline (Visit 1) results, information on lipid regulators will be collected in the same manner as described above based on the time point of the tests. Drugs administered from after the first study drug dosing to the end of observation will be collected as concomitant medication.

^6)^Height, weight and waist circumference will be measured, and body mass index (BMI) will be calculated. Height will be measured at Visit 1 only.

^7)^LDL-C, TC, TG, HDL-C, and non-HDL-C will be tested. LDL-C may be measured either directly (by homogeneous direct assay) or calculated using the Friedewald formula; when TG ≥400 mg/dL, direct LDL-C measurement is required (Section 2.7). If test results obtained within 4 weeks prior to Visit 1 are available and the participant had no treatment with lipid regulators within 4 weeks prior to the test or was treated with lipid regulators using the same dosage and administration for at least 8 weeks, the test results may be used as baseline (Visit 1) results. Before testing, a blood sample is to be collected after at least 12 hours of fasting, if possible; If it is difficult for the participant to remain fasted for 12 hours, at least 9 hours of fasting should be maintained.

^8)^If test results for HbA1c, HOMA-IR, and HOMA-β are available, the information will be collected. If it is not feasible to collect HbA1c test results within the visit window in patients with pre-diabetes or diabetes, HbA1c testing will be performed. If test results obtained within 4 weeks prior to Visit 1 are available and the participant had no treatment with lipid regulators within 4 weeks prior to the test or was treated with lipid regulators using the same dosage and administration for at least 8 weeks, the test results may be used as baseline (Visit 1) results. Before testing, at least 8 hours of fasting should be maintained.

^9)^If test results for hs-CRP are available, the information will be collected. If test results obtained within 4 weeks prior to Visit 1 are available and the participant had no treatment with lipid regulators within 4 weeks prior to the test or was treated with lipid regulators using the same dosage and administration for at least 8 weeks, the test results may be used as baseline (Visit 1) results.

^10)^Aspartate aminotransferase (AST), alanine aminotransferase (ALT), and creatine kinase (CK) are collected systematically at every visit to monitor statin-related hepatotoxicity and myopathy. If test results obtained within 4 weeks prior to Visit 1 are available, they may be used as baseline (Visit 1) results. Pre-specified safety thresholds for action: AST or ALT >3× upper limit of normal (ULN); CK >5× ULN with muscle symptoms, or >10× ULN regardless of symptoms (Section 2.4.3).

^11)^Apolipoprotein B (ApoB) is not a required measurement; it will be collected and analyzed descriptively only when available from routine clinical practice (Section 2.4.2).

^12)^Medication adherence (proportion of days covered, PDC), persistence (time from initiation to discontinuation), dose modifications, and treatment switching will be collected at follow-up visits (Section 2.4.2).

^13)^All clinically significant medical conditions or abnormalities occurring from the first study drug dosing to the EOS visit will be collected as AEs. Any unresolved AEs at the time of the participant’s EOS visit will be followed until resolution, stabilization, or for a minimum of 4 weeks after the EOS visit, whichever is later, with extended follow-up at the investigator’s discretion for serious or clinically significant events (Section 2.1).

The study protocol was approved by the ethical review board of Chungnam National University Hospital with the certificate number of 2025-07-065. This study was registered at www.clinicaltrials.gov (NCT07523971). The study protocol was developed in accordance with the SPIRIT 2013 guideline (for protocol items relevant to observational designs) and is reported according to the STROBE statement for observational studies.

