#### Safety endpoints

2.4.3

Adverse events (AEs), classified by severity (mild, moderate, severe), causality to study medication (related, possibly related, unrelated), and seriousness (serious vs. non-serious) according to ICH-E2A criteria.Laboratory tests (blood chemistry), including systematic monitoring of AST, ALT, and creatine kinase (CK) at every visit for assessment of statin-related hepatotoxicity and myopathy. Pre-specified thresholds for safety signals are: AST or ALT >3× upper limit of normal (ULN); CK >5× ULN with muscle symptoms, or >10× ULN regardless of symptoms.Vital signs.Pre-specified adverse events of special interest: hepatotoxicity, myopathy, rhabdomyolysis, new-onset diabetes mellitus, and discontinuation due to AEs.

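### The AE entry rule admits only undefined clinically significant conditions, so AE counts depend on site judgement and can be under-recorded

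*Protocol article*

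**What the plan says.** Entry rule (Table 1, footnote 13): "All clinically significant medical conditions or abnormalities occurring from the first study drug dosing to the EOS visit will be collected as AEs". The article gives no definition or criteria for clinical significance. The following sentence of the footnote covers unresolved AEs at the end-of-study visit and allows longer follow-up, at the investigator's discretion, for those that are serious or clinically significant. Section 2.1 repeats this.

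Reporting (Section 2.4.3): AEs are "classified by severity (mild, moderate, severe), causality to study medication (related, possibly related, unrelated), and seriousness". The same section lists the events of special interest: hepatotoxicity, myopathy, rhabdomyolysis, new diabetes, and stopping because of an AE.

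Laboratory endpoint (Section 2.4.3): laboratory tests are a separate item, "including systematic monitoring of AST, ALT, and creatine kinase (CK) at every visit for assessment of statin-related hepatotoxicity and myopathy". The thresholds are "AST or ALT >3× upper limit of normal (ULN); CK >5× ULN with muscle symptoms, or >10× ULN regardless of symptoms".

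Labels: footnote 10 introduces these values as "Pre-specified safety thresholds for action: AST or ALT >3× upper limit of normal (ULN") and points to Section 2.4.3, which introduces them as "Pre-specified thresholds for safety signals are: AST or ALT >3× upper limit of normal (ULN"). Section 2.1 says that treatment decisions "are made by the treating physician independently of the study".

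**The concern.** An entry rule decides what can ever be counted. Here it contains a judgement that each investigator makes without a stated criterion, in a study run across many centres with local assessment. Two sites with identical patients could report different AE rates. Compared with recording every event, such a filter can only remove events, so any distortion is downward.

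Safety is a stated objective in Section 2.1, and detection of uncommon AEs is one of the four reasons that Section 2.5 gives for enrolling 10,000 people. That reason presumes that an event that occurs is recorded. Safety is analysed on observed cases without imputation (Section 2.6.4), so no later step recovers an event that was never entered.

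**Working it through.** **1. The term is used in two ways.**

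| Place | Role of clinically significant |
|---|---|
| Footnote 13, first sentence | Condition for being an AE at all |
| Footnote 13, second sentence; Section 2.1 | Marks some AEs out from the others |

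If the first use holds, every AE is already clinically significant and the second use selects nothing. If the second use has meaning, some AEs are not clinically significant and the first sentence is not the rule in force. A site can defend either reading, and the two give different AE counts.

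**2. What the rule reaches.** It governs AE incidence by severity, causality and seriousness, and events of special interest to the extent that they are identified from AE records. It does not govern AST, ALT and CK. Table 1 requires these in all participants at all three scheduled visits, and Section 2.4.3 reports them as their own endpoint. A value above a threshold stays visible there whether or not the investigator enters an AE.

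**3. What is not stated.** No sentence says whether crossing a threshold is, by itself, recorded as an AE or event of special interest. The thresholds have the same values in both places, but one place ties them to action and the other to signals. Section 2.4.3, to which footnote 10 points, names no action.

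**4. The plan's only AE figure.** Section 2.5 claims at least 80% power at a true rate of p = 0.0004. It does not say how many events count as detection. The exact binomial chance of at least r events is P(X ≥ r) = 1 − Σ(x < r) C(n,x) pˣ(1 − p)ⁿ⁻ˣ:

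| r | n = 10,000 | n = 8,000 |
|---|---|---|
| 1 | 98.2% | 95.9% |
| 2 | 90.8% | 82.9% |
| 3 | 76.2% | 62.0% |

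The stated bound is reproduced for r = 1 and r = 2.

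**5. How much filtering that figure tolerates.** Suppose a share c of true events passes the entry rule. The documents give no c, so the range is an assumption. For r = 1, P = 1 − (1 − pc)ⁿ:

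| c | n = 10,000 | n = 8,000 |
|---|---|---|
| 1 | 98.2% | 95.9% |
| 0.8 | 95.9% | 92.3% |
| 0.5 | 86.5% | 79.8% |
| 0.25 | 63.2% | 55.1% |

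The share at which power equals 80% is c = (1 − 0.2^(1/n))/p. This gives 0.000161/0.0004 = 0.40 for n = 10,000 and 0.000201/0.0004 = 0.50 for n = 8,000. The one-event claim therefore survives moderate filtering. An incidence estimate does not have that slack, because it falls in direct proportion to c.

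**The case against.** The best defence has four parts.

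- **Severity and significance are different axes.** A mild event can be clinically significant. A reader might infer that grading mild events contradicts footnote 13, but it does not. What remains is that minor events are the likeliest to be judged not significant, so the mild category is the most exposed to site judgement.
- **Liver and muscle safety do not rest on AE entry alone.** The mandatory tests and numeric thresholds stand apart from it, and footnote 13 itself mentions abnormalities as well as conditions. A reader might infer that hepatotoxicity and myopathy are shown to be undercounted. The documents show only that AE-based counts could be low. This part of the defence stands.
- **The CK criterion does not require a recorded AE.** A reader might infer that leaving muscle pain unrecorded disables the symptomatic CK threshold. Nothing makes the symptom part depend on a prior AE entry, and a physical examination takes place at every scheduled visit. Likewise, separate reporting of laboratory crossings and clinical events is ordinary practice. The text does not prescribe counting the same event in two ways.
- **The article condenses a fuller protocol.** Case definitions for events of special interest and case report form items are commonly left there, so their absence is no finding. Treatment decisions resting with the physician also do not rule out study actions such as a query or a report, so the two threshold labels are a mismatch of wording and no more.

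The defence does not reach the entry rule itself. That rule is stated text, and a fuller document could not make its two uses of the term agree without changing one of them. The follow-up sentence may suggest that no strict filter was intended. If so, the first sentence says something the sponsor does not mean.

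**Conclusion.** The point holds as a problem of the AE entry rule. As written, it lets AE incidence and AE-based events of special interest be under-recorded to a degree that varies by site, and any effect is downward. The laboratory endpoint is untouched.

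The size cannot be derived, because the documents give neither event rates nor the share of events that sites would judge significant. The only bound available is on the detection claim in Section 2.5, and it assumes that one event suffices for detection and that a constant share of events is recorded independently across participants.

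The unstated status of threshold crossings and the two threshold labels are lesser matters of wording, to be settled in the same edit.

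**What to change.** - In footnote 13, record any untoward medical occurrence from first dose to the end-of-study visit as an AE and grade it. Keep clinical significance only as the criterion for reporting laboratory abnormalities below the pre-specified thresholds.
- State whether an AST, ALT or CK threshold crossing is by itself recorded as an AE or as an event of special interest.
- Use one label for the thresholds in footnote 10 and Section 2.4.3, and reconcile it with Section 2.1. Clinical handling stays with the treating physician.

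The change is confined to the wording of two footnotes and Section 2.4.3, with the matching instruction to sites. The downside is more minor AEs to enter and a higher reported AE rate, which the report should attribute to fuller recording.
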